##### The PTSD Checklist

The PTSD Checklist (PCL) is a well-validated 17-item self-report questionnaire that yields both a PTSD symptom severity score (possible range 17–85) and a determination of likely PTSD diagnostic status (Blanchard, Jones-Alexander, Buckley, & Forneris, 1996; Weathers & Ford, 1996). PCL items correspond to DSM-IV symptom criteria. The PCL has demonstrated strong internal consistency (*α*=0.94), test–retest reliability, and convergent and discriminant validity. The PCL has been utilized (Manne, Du Hamel, Gallelli, Sorgen, & Redd, 1998) to assess PTSD symptoms in parents of ill or injured children.

### Child health and recovery

#### The health and recovery questionnaire

This 8-item questionnaire will be used to collect information at the 12-week follow-up assessment about help-seeking and services used (health care, mental health care, informal psychosocial support) over a specified period after an index medical event (Marsac, Cirilli, Kassam-Adams, & Winston, 2011).

### Sample size

A primary goal of this RCT is to estimate effect sizes for a later full-scale RCT. Within the constraints of a pilot study, there will be reasonable power to detect a clinically meaningful effect for proximal outcomes (appraisals and coping at 6 weeks) and child health outcomes (PTSS and HRQOL at 12 and 18 weeks). With a sample of 70 participants (35 randomized to each condition), we project that we will have 60 (85%) retained to all follow-up assessments. With this sample size, a difference of 0.5 SD between conditions [based on an Analysis of covariance (ANCOVA)] with 80% power, while controlling for *α* =0.05, can be detected.

### Data analysis

ANCOVA is the primary analytic approach for examining outcomes and for initial estimation of effect sizes. ANCOVA can adjust for baseline differences between groups (intervention vs. waitlist control), as imbalances may occur despite randomization. The dependent variable in each ANCOVA will be a 6-week proximal outcome or a 12- or 18-week child health outcome, the corresponding baseline score of the outcome measure will be the covariate, and group (condition) will be the qualitative factor. Other covariates that may help explain variation in intervention effects (e.g., age, gender, prior trauma, and parent PTSS) will be considered for inclusion in these analyses. Multivariable regression analysis will also be used to examine the hypothesized role of proximal outcomes in predicting each health outcome. An intent-to-treat approach will be applied to help handle missing data.

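### Intent-to-treat is named as the remedy for missing data, but it supplies no outcome values; run as described, each single-visit ANCOVA omits children without that score and leaves earlier follow-up scores unused

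*Protocol article*

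**What the plan says.** The Data analysis section of the protocol article makes ANCOVA the main method: "ANCOVA is the primary analytic approach for examining outcomes and for initial estimation of effect sizes". Each model takes one visit: "The dependent variable in each ANCOVA will be a 6-week proximal outcome or a 12- or 18-week child health outcome". The planned adjustment is for baseline: "the corresponding baseline score of the outcome measure will be the covariate". Age, gender, prior trauma and parent PTSS may be added, but no intermediate follow-up score is mentioned. The section closes with its one sentence on missing data: "An intent-to-treat approach will be applied to help handle missing data".

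The Sample size section expects losses. Of 70 children, 35 per arm, "we project that we will have 60 (85%) retained to all follow-up assessments".

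Table 1 and the Procedure section schedule the child PTSS measure (CPSS) and the HRQOL measure (PedsQL) at baseline and at 6, 12 and 18 weeks. A 6-week score for both health outcomes is therefore collected, although the health outcomes are analysed only at 12 and 18 weeks.

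**The concern.** Intent-to-treat answers which children belong to the comparison and in which arm each one counts. It gives no value, model or assumption for a child whose outcome was not obtained. The article assigns it a task that it cannot perform. This is different from leaving imputation detail to an analysis plan: a remedy is named, and it is the wrong kind of remedy.

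With nothing else specified, a single-visit ANCOVA uses only the children who have that visit's score. A child assessed at week 6 and then lost contributes nothing to the 12- or 18-week PTSS and HRQOL estimates, although a relevant score is on file.

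The trial's stated purpose is to estimate effect sizes for a later full-scale trial, so a bias here would carry into that trial's sample size. Dropout that differs by arm is plausible. Families know their condition, the intervention arm receives weekly reminders up to week 6, and the waitlist arm gets access only after the 12-week assessment. The documents do not say that such dropout will occur.

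**Working it through.** **1. The plan's own figure.** 60/70 = 85.7%, and 0.85 × 70 = 59.5, so 60 (85%) reproduces. Then 70 − 60 = 10 children, or 10/70 = 14.3%, are projected to miss at least one of three follow-ups. Ten is thus an upper limit for any single visit. It is reached at week 18 if children who leave do not return, and may be smaller at weeks 6 and 12.

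**2. Which scores could be used.**

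| Outcome | Analysed at | Earlier follow-up score collected |
|---|---|---|
| Appraisals, coping | 6 weeks | none |
| PTSS, HRQOL | 12 weeks | 6 weeks |
| PTSS, HRQOL | 18 weeks | 6 and 12 weeks |

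Only children lost after week 6 have an unused follow-up score.

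**3. Possible bias.** The article gives no correlations and no dropout mechanism, so these are assumptions:
- correlations: baseline to week 6, 0.55; week 6 to week 12, 0.65; baseline to week 12, 0.50;
- true effect -0.50 SD, the size the article uses for power, assumed at weeks 6 and 12;
- about 14% dropout after week 6, logistic in the 6-week score.

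Compared are ANCOVA on observed 12-week scores and the same model after regression imputation from baseline, arm and 6-week score. The imputation stands in for a repeated-measures model or multiple imputation.

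| Dropout pattern | Observed scores only | Using 6-week scores |
|---|---|---|
| Random | about -0.50 | about -0.50 |
| Rises with symptoms alike in both arms | -0.50 to -0.51 | about -0.50 |
| Depends on symptoms in the intervention arm only (odds ratio about 1.6 to 2.7 per SD) | about -0.53 to -0.55 | about -0.50 |
| Opposite directions by arm, odds ratio about 1.6 per SD | about -0.55 | about -0.50 |
| Opposite directions by arm, odds ratio about 2.7 per SD | about -0.60 | about -0.50 |

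In the last two rows, children with more symptoms leave the intervention arm and children with fewer symptoms leave the waitlist arm. Reversing both slopes reverses the bias, so -0.60 becomes about -0.50 + 0.10 = -0.40.

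Recovery to -0.50 is built in, because dropout was made to depend only on the 6-week score that the imputation uses. The table shows what the remedy can correct, not that it corrects every mechanism.

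**4. Bias against noise.** With random dropout, the variance of the observed-score estimate in simulated trials of 35 per arm was 0.0504, so the standard error is √0.0504 = 0.22. The largest bias in the table is 0.10/0.22, or about 0.45 of a standard error.

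**5. Precision.** The squared partial correlation of the 6- and 12-week scores given baseline is

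R² = [(0.65 − 0.55 × 0.50)]² / [(1 − 0.55²)(1 − 0.50²)] = 0.1406/0.5231 = 0.27.

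With m dropouts who have a 6-week score, effective N ≈ 1/[(1 − R²)/60 + R²/(60 + m)]. For m = 5 this is 61.3; for m = 10 it is 62.4. Other plausible correlations give about 61 to 64, against 60 without the 6-week scores. In simulation with random dropout the variance fell from 0.0504 to 0.0481, or 4.6%; a second run gave about 3%.

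**The case against.** The strongest reply is that a journal article condenses the plan, and imputation methods are normally left to the analysis plan. The article never says completers only and never excludes imputation. This stands in part. A reader might infer that the trial commits itself to a complete-case analysis; the text does not say so. That analysis is what follows by default from the method described, and an unseen plan could add to it. The sentence would still name intent-to-treat as the handling of missing data, which is wrong in any version of the plan.

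A reader might also take the 60 in the Sample size section as a declared analysis set. It is an attrition allowance, compatible with any missing-data method.

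Other stronger readings fail too. The documents do not support saying that ten children drop out of every analysis, or that all ten have 6-week scores. For 6-week appraisals and coping there is no earlier follow-up to borrow from. A claim that the effect will be overstated by 20% rests on one strong pattern, with symptom-related dropout running in opposite directions in the two arms. Under dropout that is random or alike in both arms there is practically no bias.

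Finally, baseline-adjusted ANCOVA is a legitimate estimator for a 70-child pilot, the precision gain is small, and even the largest bias shown is under half a standard error. All true. The case rests on protection against arm-dependent dropout at almost no cost, in a trial whose effect estimate is meant to be reused.

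**Conclusion.** The point holds and should be corrected before analysis. The article names a remedy for missing data that cannot supply what is missing. As described, each ANCOVA omits children without that visit's score, at most about 10 of 70 at any visit, and the 12- and 18-week PTSS and HRQOL models leave earlier follow-up scores unused for children lost after week 6.

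The possible bias is moderate and conditional: about 0.03 to 0.10 SD on a 0.50 SD effect if dropout depends on 6-week symptoms differently by arm, and essentially none otherwise. The loss of precision is about 3-5%. The omission itself follows from the text; the bias figures rest on the assumed correlations, dropout rate and dropout slopes above. The point does not depend on whether the article's power statement is right.

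**What to change.** Separate the two ideas in the Data analysis section.

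- **Analysis set:** all randomised children, each in the assigned arm.
- **Missing PTSS and HRQOL scores:** either a likelihood-based repeated-measures model over baseline, 6, 12 and 18 weeks with baseline modelled as an outcome, or multiple imputation by arm that includes baseline and earlier follow-up scores. Both keep children with no follow-up at all; a mixed model with baseline only as a covariate would drop them. Arm differences are reported at 12 and 18 weeks, as now planned.
- **Missing 6-week appraisals and coping:** only baseline data can inform the imputation, and the text should say so.
- **Assumption:** state missing at random given the observed scores, and add a sensitivity analysis that departs from it, for example by shifting imputed scores by a fixed amount in one or both arms.

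The cost is a little more analysis work; no new data, visits or participants are needed. The remaining drawback is reliance on missing at random. That assumption is weaker than the one behind the observed-score ANCOVA, because it may also condition on earlier follow-up scores, but it cannot be verified from the data.

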## Discussion

The high prevalence and significant impact of acute traumas on children's functioning warrant innovative approaches of delivering effective secondary prevention of psychosocial sequelae. Coping Coach translates research on etiology and malleable risk and protective factors into a novel web-based intervention. The intervention integrates evidence-based components of CBT techniques and Internet interventions, applying these to prevention by targeting early appraisals, coping, and support-seeking. Coping Coach is designed to require interaction with the game content to facilitate engagement and learning. The current RCT will provide us with pilot data to prepare for a larger-scale evaluation of Coping Coach. Specifically, this study will examine the feasibility of the Coping Coach intervention as well as the study procedures. In addition, the current RCT represents a unique opportunity to estimate the efficacy of Coping Coach in promoting positive child health outcomes and preventing or reducing negative psychological sequelae. Toward this goal we will examine proximal outcomes of appraisals and coping along with long-term child health outcomes, PTSS and HRQOL. We expect that the results of this RCT will augment the existing literature by producing new information (pilot data) on the effectiveness of web-based preventive interventions for children after acute medical trauma.

Among the strengths of this study is its incorporation of assessments with both children and parents to evaluate clinically meaningful short- and long-term effects of Coping Coach. Data from this RCT will help to refine our program theory and potentially modify existing conceptual models for the development of psychological symptoms after an acute medical event (i.e., hypothesized etiological mechanisms). This RCT will also enable us to estimate effect sizes for proximal and child health outcomes and inform modifications of Coping Coach prior to a larger scale trial. The electronic tracking built into the study design allows us to examine actual completion of the intervention modules to determine if there is a necessary minimum intervention “dose” and allows us to evaluate how children interact with game content. Finally, this RCT will allow us to evaluate factors that may impact child engagement and adherence and to identify ways to increase potency of intervention effects.

Possible limitations of this RCT include technical difficulties that may be experienced by participants. To meet this challenge, we have worked to ensure accessibility and functionality of the intervention. Another potential limitation is that some participants may not finish all intervention modules after discharge from the hospital. We will attempt to minimize this by sending tailored, weekly reminders to children and families and providing a small incentive for children who complete all Coping Coach modules. In addition, we will track the completion of the intervention electronically, so that we will be able to determine what intervention components were completed by each participant. Other potential limitations include recruitment challenges or possible sampling bias. We will attempt to prevent this by closely monitoring weekly recruitment and retention rates. We will adjust strategies as needed to achieve recruitment targets, and address any significant deviations of sample demographics from the pool of eligible patients.

If results suggest that Coping Coach can prevent emotional sequelae and improve child health outcomes, the intervention would provide a promising avenue to help children cope in the aftermath of a traumatic medical event. Given its web-based modality, Coping Coach can provide widely accessible tools to promote positive child health outcomes. In addition, Coping Coach could be provided as a resource that physicians, mental health professionals, social workers, and teachers could recommend for children at risk for PTSS.
